#### Participants

Participants who complete the virtual ABC program will be recruited from all sites to participate in qualitative interviews provided they are able to communicate fully (English proficiency, non-severe aphasia). It is expected that 15–20 participants will be eligible and interviewed virtually and will depend on when data sufficiency is reached, and identified themes do not need to be adjusted by further data collected [23].

#### Procedures / Data collection

Individual semi-structured interviews will be conducted online using Zoom software. Interviews will be conducted within 2 months of participants completing the V-ABC program. Interviews will be conducted by a trained researcher with qualitative experience, who is not involved in the care of the participant. Interviews will last approximately 60 min and will be audio-recorded.

The semi-structured interview guide was developed by one of the authors ([name]) and reviewed by two physical therapists, two occupational therapists, two individuals with stroke and an engineer who was involved in the development of the TENZR activity monitor (Appendix 1). The development of the interview guides was informed by the Capability, Opportunity, Motivation, Behaviour Model to understand the mechanisms of changes within a behaviour change intervention [15]. This model positions behaviour as the product of an interaction between three components: capability, opportunity and motivation [15]. Questions aim to identify relevant components of the virtual ABC program which contribute to its effectiveness.

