**Methods:**

This mixed-methods study will utilize a prospective controlled trial with random allocation to immediate or 3-week delayed entry to determine the efficacy of a 3-week behaviour change program with a nested qualitative description study. The intervention, the Virtual Arm Boot Camp (V-ABC) features feedback from a wearable device, which is intended to increase upper limb use post stroke, as well as 6 virtual sessions with a therapist. Sixty-four adults within 1-year post stroke onset will be recruited from seven rehabilitation centres. All outcomes will be collected virtually. The primary outcome measure is upper limb use measured by grasp counts over 3 days from the wearable sensor (TENZR) after the 3-week intervention. Secondary outcomes include upper limb function (Arm Capacity and Movement Test) and self-reported function (Hand Function and Strength subscale from the Stroke Impact Scale). Outcome data will be collected at baseline, post-intervention and at 2 months retention. The qualitative component will explore the experiences and acceptability of using a home program with a wearable sensor for increasing arm use from the point of view of individuals with stroke. Semi-structured interviews will be conducted with participants after they have experienced the intervention. Qualitative data will be analysed using content analysis.

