##### Follow-up sessions

Participants will be asked to take part in five follow-up sessions virtually after the initial session to monitor their adherence to the exercise program, ability to meet daily movement targets and to progress their exercises and movement targets. At the second session, the therapist will set daily movement targets in collaboration with the participant based on the average daily hand counts captured by the TENZR based on the baseline counts, as well as counts since the initial session. See the “Evaluations” section for the definition of a hand count. The following suggested guidelines will be provided to therapists for setting daily movement targets. If the daily baseline hand counts are less than 1000, then a target for 1000 daily hand counts will be set. If the daily baseline hand counts are greater than 1000, an additional 20% will be added. A minimum of 1000 hand counts will be set. Therapists may modify the exercises and daily activities to accommodate fatigue and/or pain.

The tablet will show the daily total GRASP counts and participants will then record these values in a 1-page summary sheet and review with their therapists at each session. Therapists will prompt participants to identify barriers to meeting movement targets and will assist participants to problem solve solutions to overcoming those barriers. The logging of the GRASP counts and discussion of strategies to increase GRASP counts will serve as a mechanism of accountability and adherence to the protocol. At the final session, the therapist will discuss recommendations for further arm activity.

The components of the V-ABC were designed to address considerations outlined in the Capability, Opportunity, Motivation, Behaviour Model applied to affected upper limb use after stroke [14]. This is a model of behaviour described in the Behaviour Change Wheel Framework [15]. The framework helps guide the development of behaviour change interventions. Table 1 outlines the Capability, Opportunity, Motivation, Behaviour Model applied to the affected upper limb use during daily activities. The information for this table was obtained from the literature and through our experience studying upper limb use post stroke.

**Table 1 Tab1:** Capability, Opportunity, Motivation, Behaviour Model Components of the intervention

What needs to happen so that the affected arm is used?	Methods to address components

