**Capability: Psychological**	
• Understands the evidence related to experience-driven neuroplasticity • Understands the importance of “use it or lose it”; • Understands the importance of challenge and practice • Has emotional resilience to practice despite frustration • Has ability to problem solve when encountering problems using the limb • Has ability to monitor how and how much they are using limb • Knows how to advance task practice • Patient has sufficient memory/attention/executive function to develop and adhere to practice schedule	• Education of link between challenging practice and neuroplasticity • Feedback from TENZR • Action planning • Goal setting • Barrier identification and problem solving

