#### Evaluations

Participants randomized to the immediate treatment group will undergo 3 assessments through Zoom software: (1) upon admission to the study (baseline assessment), (2) immediately following completion of the treatment (post-intervention) and (3) 2 months following completion of the treatment (retention). Participants randomized to the delayed treatment group will undergo 4 assessments: (1) upon admission to the study (baseline assessment), (2) 3 weeks post baseline, (3) immediately following treatment (post-treatment) and (4) 2 months following completion of the treatment (retention). Evaluators will be occupational or physical therapists who will participate in about 4 h of training (reviewing materials and an online training session). They will be blinded to group allocation of the participant, i.e. immediate vs delayed. Participants will be instructed not to reveal their group to the evaluator. See Table 2 for the schedule of enrolment and timing of the evaluations.

**Table 2 Tab2:** Schedule of enrolment and evaluations

Study procedures	Screening	Baseline evaluation	Post-intervention evaluation	Two-month evaluation
Timepoint	− *T*_1_	*T*_0_	*T*_1_	*T*_2_
Informed consent	+			
Inclusion/exclusion criteria	+			
Demographics		+		
Randomization		+		
Primary outcome measure				
3-day hand counts		+	+	+
Secondary outcome measures				
Impairment				
Upper limb pain		+	+	+
Functional				
Arm Capacity and Movement Test (upper limb functional capacity)		+	+	+
REACH Scale (self-reported arm use)		+	+	+
Stroke impact scale—arm function		+	+	+
Stroke impact scale—arm strength		+	+	+
Adverse events		+*	+*	+*

*indicates that the measure will be taken or monitored throughout the intervention period

Participants will be reminded about follow-up appointments at each appointment, in addition to a reminder immediately before the appointment by phone, text or email, depending on the participant’s preference. In addition, a secondary contact of the participant will be collected in case the participant cannot be contacted at their primary contact number.

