  Prompt: How was incorporating your affected arm and hand in daily activities discussed during the therapy sessions? What daily activities, if anything, did you do to increase the hand counts?
  Prompt: During the 3-week program, the activity monitor showed the number of hand counts over the course of an average day. To what extent, if any, do you think your hand counts were due to the GRASP exercises?
  Prompt: To what extent, if any, do you think your hand counts were due to using your affected arm during the rest of the day (during daily activities outside of GRASP exercises)?
  Prompt: What did you think about the idea that using your affected arm during daily activities is therapy?
10. The therapy sessions were delivered virtually using videoconferencing technology (e.g. Zoom, webcam, computer, headphones, etc.). What was your experience with the virtual aspect of the sessions?
  Prompt: What had been your experience with using videoconferencing for therapy sessions before the study?
  Prompt: How do you feel about using videoconferencing for therapy sessions now?
  Prompt: What, if anything, worked well with the virtual sessions?
  Prompt: How, if at all, could it be improved?
  Prompt: What are your thoughts on using videoconferencing technology for therapy sessions beyond this trial for yourself?
11. What do you think about your family or caregiver’s involvement in the Arm Boot Camp program?
  Prompt: What was your family or caregiver’s role in this program?
  Prompt: What, if anything, worked well with their involvement?
  Prompt: How, if at all, could it be improved?
12. What was your experience trying to continue doing exercises with your affected arm after the Arm Boot Camp 3-week program was over?
  Prompt: What, if any, exercises do you do now with your affected arm? (If they say they are doing exercises now for their affected arms, clarify if the exercises are the GRASP exercises or include some of the GRASP exercises.)
  Prompt: How much exercise do you do now with your affected arm?
  Prompt: How much do you now use your affected arm during daily activities?
  Prompt: What, if any, were some of the barriers to doing exercises for your affected arm after the program was over?
  Prompt: What, if anything, helped you continue doing exercises for your affected arm after the program was over? (if appropriate)
13. Is there anything that you would like to say but did not get a chance to say?

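### The interview window fills the interval before the 2-month retention assessment, so interviews may prompt arm use or shift self-report just before retention is measured (minor)

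*Protocol article*

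**What the plan says.** **Interview timing and content.** Procedures / Data collection (qualitative component) says "Interviews will be conducted within 2 months of participants completing the V-ABC program". It sets one session of roughly an hour, led by a researcher outside the participant's care. The Participants section of the same component restricts interviews to people who completed the program and can communicate fully, and gives the number: "It is expected that 15–20 participants will be eligible and interviewed virtually". The guide in Appendix 1 shows the sensor again. It asks how targets progressed, how much the participant now exercises and uses the arm, and what they think of daily use as therapy. It also asks: "What, if any, were some of the barriers to doing exercises for your affected arm after the program was over".

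**Retention timing.** For both groups, Evaluations places the last assessment "2 months following completion of the treatment (retention". Table 2 lists hand counts, pain, the Arm Capacity and Movement Test, REACH and the two Stroke Impact Scale subscales at that visit. Data analyses assigns retention to an additional mixed effects model.

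**Program content.** Follow-up sessions says "Therapists will prompt participants to identify barriers to meeting movement targets", and therapists then help to solve them. Table 1 lists "Barrier identification and problem solving" among the methods of the intervention.

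The article does not say that the retention assessment comes first, or how interviewees are handled in the retention analysis.

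**The concern.** The outcome is a behaviour, and talking about that behaviour at length can change it. The interview guide and the intervention were built on the same behaviour model, and several interview topics match what therapists covered. If the conversation takes place in the weeks before the 3-day wear, it may act as a reminder to use the arm. It may also change how participants answer REACH and the Stroke Impact Scale, because the guide asks directly about current arm use.

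The protocol guards against prompting elsewhere: it switches off the sensor's feedback during assessment wear. The interview has no such safeguard.

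What is at stake is the 2-month question. By then both groups have received the program and no untreated group remains, so whether gains persist is judged largely within person. Spreading interviews evenly over the two groups would not remove an interview effect from that estimate.

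**Working it through.** **1. Timing side by side.**

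| Event | Anchor | Time allowed |
|---|---|---|
| Interview | completion of V-ABC | any time up to 2 months |
| Retention assessment | completion of treatment | at 2 months |

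Anchor and length are the same. An interview inside its window therefore falls before the retention assessment or around the same time. It can follow the assessment only if that visit is early or the interview falls at the very end of the window. The guide's introduction mentions that evaluation sessions have taken place, but this does not settle the order, because the baseline and post-treatment visits already satisfy it.

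**2. Which analyses are exposed.**
- *Primary outcome:* average daily hand counts immediately after the 3-week intervention. Interviews require completion of the program. Delayed-group participants have not had it at their 3-week assessment, so they cannot yet be interviewees. Not exposed.
- *Secondary outcomes at post-treatment:* same time point and analysis. Not exposed.
- *Retention model:* exposed.

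**3. Share of participants interviewed.** Inputs: 15 to 20 interviewees (qualitative Participants section); 64 recruited (Abstract, Methods: "Sixty-four adults within 1-year post stroke onset will be recruited from seven rehabilitation centres"); 20% dropout (Sample size estimates).

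The planned total reproduces. With ANCOVA, two groups, one covariate, f = 0.4 and two-sided 0.05, the smallest total N with at least 80% power is 52 (power 0.807). Allowing for dropout gives 52/0.8 = 65, or 52 × 1.2 = 62.4, rounded up to 63. Both are within 2 of 64. The sample size is not in dispute; 64 and 20% serve only as denominators.

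- Of all randomized: 15/64 = 23.4%; 20/64 = 31.3%.
- After dropout: 64 × 0.8 = 51.2, about 51; 15/51 = 29.4%; 20/51 = 39.2%.

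**4. Possible shift in the retention mean.** The documents give no interview effect, so it is assumed over a range. Shift = (share interviewed) × (effect in interviewees), taking every interview to precede the retention wear.

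| Assumed effect in interviewees | Lowest share (15/64) | Highest share (20/51) |
|---|---|---|
| 0 | 0 | 0 |
| 0.1 SD | 0.02 SD | 0.04 SD |
| 0.2 SD | 0.05 SD | 0.08 SD |
| 0.5 SD | 0.12 SD | 0.20 SD |

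**The case against.** The strongest reply is that a research interview is not therapy. The interviewer sets no target and gives no advice, sensor feedback or help with solving problems. The program pairs naming barriers with working out solutions; the guide does only the first, in one prompt among many about past experience, the technology and the caregiver's role. This stands, and it makes a large effect less likely. It does not exclude reactivity, since talking about current use and barriers can be a cue by itself.

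A second reply is that the protocol never promises an interval free of contact. Therapists give recommendations for further activity at the last session, adverse events are followed through to the 2-month visit, and everyone wears the sensor again at retention. This also stands. But those cues reach all participants, whereas the interview reaches a selected minority.

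A third reply is that early interviews protect recall of a 3-week program. That is a real trade-off, though the present window already accepts recall of up to 2 months.

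A reader might infer that the interviews contaminate the retention outcome and inflate apparent retention. The documents do not support that. They show an overlap in timing and topic but no evidence of an effect. The direction is also open: prompting would raise counts, while reflecting on barriers could lower self-ratings. Nor do they support a bias between groups, which would need unequal interviewing by arm; nothing in the article indicates that.

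**Conclusion.** The point holds as a risk, of minor severity. As scheduled, interviews will usually come before the retention measurement and cover topics close to the program's own content, for roughly a quarter to two fifths of those contributing data. Only the additional 2-month analysis is exposed.

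The size is unknown. The range of 0.02 to 0.20 SD rests entirely on an assumed effect of 0.1 to 0.5 SD in interviewees and on all interviews preceding the wear. With no interview effect, or with all interviews held after the retention assessment, the shift is 0. The reason to act is that the risk is easily avoided, not that harm has been shown.

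**What to change.** Change the timing sentence in Procedures / Data collection so that interviews take place shortly after the 2-month assessment and its 3-day wear are both complete. At publication about half the participants had been recruited, so the change could still cover many interviews.

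For interviews already held, record the date relative to the retention wear and add a sensitivity analysis of retention by interview status. Read it with care: interviewees are completers who communicate fully, so a difference from the others would mix selection with any interview effect. Reordering is therefore the better remedy.

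The cost is a small amendment to the text and somewhat older recall of the 3-week program. The questions on continuing exercise after the program would gain from the later date.

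Suggested wording: *Interviews will be held shortly after the participant has completed the 2-month assessment, including the 3-day sensor wear. The dates of the interview and of the wear period will be recorded.*

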#### Data processing and analysis

All interviews will be transcribed verbatim and analysed using conventional content analysis [24]. Transcripts will be read and re-read to ensure familiarization with the data. Statements will be inductively coded to initial codes that encompass the meaning of the statement by two investigators. The initial codes will then be iteratively consolidated and grouped into broad categories, which will then be used to develop common themes. Through an iterative process, themes and interpretations will be refined to provide an understanding of how the virtual ABC program is perceived by the participants.

#### Trustworthiness

Several strategies will be used to ensure the trustworthiness of this qualitative component of the study. Investigator triangulation will be applied by involving several researchers in the process of data analysis to support the credibility of the qualitative findings. Regular analytical sessions will be held within the research team to compare interpretations and resolve the differences. Negative case analysis and participant checking will also be used to enhance credibility. The synthesized data will be presented to the participants to check for accuracy and resonance with their experiences. If any additional data were to be added during this process, it will be cross-referenced with existing codes and integrated into the analysis [25]. Furthermore, interpretation of the qualitative data alongside the quantitative findings will also enhance the credibility of this study. Research reflexivity will be facilitated by keeping a reflexive journal to support the transferability of the qualitative findings. Reflections on any assumptions, power differentials (e.g. between participant and interviewer) and interpersonal dynamics that come up during interviews that may affect data collection will be noted to account for the positions of the interviewers and personal assumptions [26]. In addition, information regarding research context, processes, participants, context and researcher-participant relationships will be provided to allow the reader to evaluate the rigour and transferability of the study.

#### Knowledge translation

The data collected in this study will be used for journal publications and presentations to clinicians, researchers and the public. Participants will receive trial outcome information if requested.

## Discussion

The integration of wearable sensors with rehabilitation programs is in its infancy. There have been some programs which utilize heart rate monitors and step counters to set targets to improve walking or physical activity after stroke [27, 28]. However, the use of monitors for the upper limb treatment after stroke are less common. Sanders et al. [29] used a grip sensor integrated with a musical computer game (MusicGlove) to encourage hand use after stroke. Da-Silva et al. [10] showed preliminary results on using a wrist-worn accelerometer which vibrated when arm activity levels were low. The integration of a sensor to monitor upper limb use may be ideal for home programs. When home programs are prescribed during rehabilitation, it is difficult for the therapist to determine how much practice is actually occurring. While a patient can document the minutes of practice, one person could practice 30 min with a few hundred repetitions, while another could do a thousand repetitions. Additionally, the use of a wearable sensor can provide valuable objective data with respect to incorporation of the affected upper limb into ADLs throughout the day, a critical piece to optimizing functional gains. As the Capability, Opportunity, Motivation, Behaviour Model illustrates [14, 15], changing behaviour is complex. In our study, feedback from the sensor can provide accountability, as well as motivation for the number of repetitions that the patient is undertaking in their home program and in daily use. The proposed protocol is innovative in focusing on use as the primary outcome. Ultimately, the goal of rehabilitation is to improve use of their arm in everyday life, and not just in the clinic.

There are many reasons why the development of evidence-based virtual rehabilitation programs is needed. The COVID-19 pandemic has highlighted the benefits of virtual care as hospital programs experienced restricted caseloads due to the risk of on-site COVID-19 transmission. A program like V-ABC can be delivered at home without risk to COVID-19. Many rehabilitation programs quarantined patients to their room for a period of time to reduce the potential for infection. Social distancing requirements reduced the space available to treat patients, and notably, permitted caseloads were reduced. We previously showed the feasibility of using a virtual arm and hand rehabilitation protocol in a small pretest-posttest study to improve arm function without any specialized equipment or technology except for the communication device itself (computer, tablet, smartphone) [30]. Beyond COVID-19, evidence-based virtual programs have appeal. They increase the reach of a program, especially to rural and remote locations. It has been documented that people living in rural regions have less chance of receiving physical therapy or occupational therapy after a stroke [31]. Treatment in the home also provides a convenience to the patient. Lastly, there may be cost-savings in having a virtual program at the home of a patient. The patient does not need to travel to the hospital, nor does the therapist need to travel to provide home therapy, and caseloads are not restricted by space.

This study uses a mixed-methods approach to study the efficacy and acceptability of this program. It is important to understand the experience of the patient in utilizing a wrist-worn sensor, in conjunction with an exercise program. Understanding the barriers and facilitators to the protocol will facilitate implementation if the protocol demonstrates efficacy.

This study has several limitations. We anticipate individuals with mild to moderate stroke severity to be eligible, while those with severe stroke who have little hand or arm movement would not be eligible.

